#### SPADI Measurement

The pain scale and disability score will be decided based on a questionnaire administered by the researcher to the participants [30], as shown in Multimedia Appendix 1. Verbal anchors for the pain dimension are “no pain at all” and “worst pain imaginable,” and those for the functional activities are “no difficulty” and “so difficult that it required help.” The scores from both dimensions are averaged to derive a total score.

#### Interpretation of Scores

The total pain score as a percentage is calculated using the following formula: total obtained score / 50 × 100. If a participant does not answer all questions, the score is divided by the total possible score (eg, if 1 question is missed, the score is divided by 40).

The total disability score as a percentage is calculated using the following formula: total obtained score /80 × 100. If a participant does not answer all questions, the score is divided by the total possible score (eg, if 1 question is missed, the score is divided by 70).

The total SPADI score as a percentage is calculated using the following formula: total obtained score /130 × 100. If a person does not answer all questions, the score is divided by the total possible score (eg, if 1 question is missed, the score is divided by 120) The means of the 2 subscales are averaged to produce a total score ranging from 0 (best) to 100 (worst).

#### McGill Pain Questionnaire

The McGill Pain Questionnaire assesses pain through 3 components: sensory, affective, and evaluation dimensions [31]. Patients select descriptors that match their pain experience, and pain is related to intensity using a present pain intensity scale. Results are interpreted by summing the pain rating index.

### Participant Timeline With Deliverables

Table 5 outlines the study’s timeline, highlighting each phase’s duration and overlapping activities systematically. The total study period is 24 months, including preparatory work, recruitment, intervention, follow-up, and analysis and comprises 3 cycles (ie, 1-3.5 months for the drugs), including buying the drugs. Recruitment of the staff, procuring the equipment, and finalizing the case report form (CRF), among other related activities, were completed in the initial phase, not throughout the full 24 months. Participants will be recruited over 16 months, the treatment period will last 7 days, and the last follow-up will be on the 32nd day. Data compilation, analysis, report preparation, and publication will be conducted during the last 3 months.

**Table 5. T5:** Gantt chart.

Step	Quarter							
	1	2	3	4	5	6	7	8
Approval from IEC^a^	✓							
Review of the literature		✓						
Drug preparation			✓					
Enrollment of patients				✓	✓			
Data collection				✓	✓			
Statistical analysis				✓	✓			
Thesis writing						✓		
Submission						✓		

a IEC: institutional ethics committee.

### Sample Size

#### Formula Using Mean Difference

The sample size was calculated based on pilot study data due to the absence of larger studies on this topic as follows:

$n_{1}=n_{2}=2\cdot \frac{(Z_{\alpha }+Z_{\beta }{)}^{2}\sigma^{2}}{(\delta {)}^{2}}\;\begin{array}{ll} Z_{\alpha }=1.96 & \text{at 5\textbackslash{}\% error \textbackslash{}§amp; CI at 95\textbackslash{}\%}\\ Z_{\beta }=0.84 & \text{Power at 80\textbackslash{}\%} \end{array}$

#### Primary Variable: Abduction Improvement

The primary variable, shoulder abduction improvement, was used to calculate the minimum sample size required for the study, ensuring adequate power to detect a meaningful difference between groups. The primary variable in this study is shoulder abduction improvement, measured as the increase in the range of motion after the intervention. Based on expected differences, variability, significance level, and power, the minimum sample size required was calculated to ensure reliable detection of a meaningful improvement

Where the mean score for abduction in *shudhabala taila nasya* pre=2.23 (as per the study by Revathi et al [22]).

Mom score for abduction in *shudhabala taila nasya* post at follow-up=1.06.

Difference (pretest-posttest)=1.17

SD=0.58.

Considering 45% superiority in the thermal microcautery group=(1.17) × 45 = 0.526

Mean differenсе *δ*=0.526

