#### Normal ROM of the Shoulder Joint

The goniometer measures the shoulder’s ROM before and after treatment [29].

Flexion, extension, abduction, adduction, and internal and external rotation are possible shoulder movements, and the normal readings for these movements are shown in Table 4.

**Table 4. T4:** The regular movements and readings for the shoulder joint.

Movement	Normal reading (degrees)
Flexion	180
Extension	50
Abduction	180
Adduction	50
Internal rotation	90
External rotation	90

All the ROM measurements will be taken in a standing position, and the participant will be instructed to place the back of the head, back and buttocks, and heels against the wall to prevent the trunk from moving. Each movement will be measured 3 times on a goniometer at the glenohumeral joint to avoid human error, and the average of 3 readings will be calculated and recorded.

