#### Minimum Sample Size Required

Based on expected differences, variability, significance level, and power, the minimum sample size required was calculated to ensure reliable detection of a meaningful improvement:

n=1=2=2 × (1.96 + 0.84)^2^ × (0.58)^2^/(0.526)^2^=20 per group

Total samples = 20 × 3 per group=60

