### Data Collection Plan and Management

All the details entered in CRFs will be collected, and each participant will be provided with a unique enrollment number. The signed consent forms, along with the CRFs, will be placed in locked cabinets, and all electronic data will be password protected. Data access will be limited to the principal investigator and coinvestigator during and after the study. For dropouts, 10% of the data will be imputed using proper techniques, and efforts will be made to collect data for at least 1 month after enrollment.

Emergency unblinding will be conducted only if necessary for the participant’s safety or clinical management. If needed, the investigator will follow the emergency unblinding procedure. The allocation will not be revealed to the participant or study personnel unless necessary for patient care. All unblinding events will be recorded in the CRF.

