### Statistical Methods

One-way ANOVA will be applied to compare the means of the 3 groups. If ANOVA indicates a significant difference, post hoc tests will be further applied (eg, the Tukey honestly significant difference test) to identify which group differs. A *P* value of <.05 will be considered statistically significant. Covariates such as age and baseline severity will be considered, and adjustments will be made using analysis of covariance if needed. The analysis will be intention to treat, with missing data handled through multiple imputation. Statistical assistance will be provided by a statistician or someone skilled in statistics. We will use SPSS (version 26; IBM Corp) for statistical analysis.

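### The 80% power claimed for 20 per group belongs to one unadjusted two-group test on an abduction score; for the same pair the planned ANOVA-then-Tukey route gives about 67%, and no power is shown for abduction in degrees

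*Protocol article*

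**What the plan says.** All references are to the Protocol article.

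- **Formula Using Mean Difference** gives the two-group formula for a difference in means, with 1.96 for a two-sided 5% level and 0.84 for 80% power.
- **Primary Variable: Abduction Improvement** takes its inputs from an earlier study of the nasal oil, where the mean abduction score went from 2.23 to 1.06: "Difference (pretest-posttest)=1.17", SD 0.58. The difference to detect is "Considering 45% superiority in the thermal microcautery group=(1.17) × 45 = 0.526". The section says that this variable "was used to calculate the minimum sample size required for the study, ensuring adequate power to detect a meaningful difference between groups", and defines it as a gain in range of motion after the intervention.
- **Minimum Sample Size Required** gives "2 × (1.96 + 0.84)^2^ × (0.58)^2^/(0.526)^2^=20 per group", multiplies by three to reach 60, and says that "the minimum sample size required was calculated to ensure reliable detection of a meaningful improvement". It makes no allowance for multiplicity or for loss to follow-up.
- **Statistical Methods** plans a one-way ANOVA on the three means at P<.05. If it is significant, "post hoc tests will be further applied (eg, the Tukey honestly significant difference test) to identify which group differs". Analysis is by intention to treat with multiple imputation, and covariate adjustment is used only if needed.
- **Data Collection Plan and Management** says "For dropouts, 10% of the data will be imputed using proper techniques".
- **Normal ROM of the Shoulder Joint** says "Each movement will be measured 3 times on a goniometer at the glenohumeral joint". Its Table 4 gives normal abduction as 180 degrees.
- **Anticipated Findings** (Discussion) states the hypothesis that microcautery will do better than both other arms.

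**The concern.** The test used to size the trial is not the test that will be run. The sizing formula treats microcautery against nasal oil as the only comparison, at an unadjusted 5% level. The analysis plan requires a significant three-arm ANOVA and then, if Tukey is used, a larger critical value for each pair. Power for that pair must then be below 80%, and the article says nothing of this.

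The inputs are also on a different scale from the outcome. A score that drops from 2.23 to 1.06 with improvement, with SD 0.58, cannot be abduction in degrees, which rises with improvement towards 180.

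What is at stake is interpretation. Readers are told that the trial is adequately powered. If it has about a one-in-three chance of missing the assumed difference for the sized pair, a non-significant pairwise result is weaker evidence than the stated power suggests.

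**Working it through.** **Inputs.** Difference 0.526 and SD 0.58 (Primary Variable: Abduction Improvement); 20 per group in three groups (Minimum Sample Size Required); 1:1:1 allocation (Randomization and Allocation); ANOVA, then Tukey, at 5% (Statistical Methods). A is microcautery, B physiotherapy, C nasal oil.

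**1. The plan's own figure.** 0.45 × 1.17 = 0.5265, used as 0.526; the printed 45 is a percentage. Then 2 × (1.96 + 0.84)² × 0.58² / 0.526² = 19.06, which the plan takes up to 20. At n = 20 an unadjusted two-sample t test has 79.8% power (81.8% by normal approximation). The stated figure reproduces.

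**2. Power of one Tukey comparison, A against C.** The standardised difference is 0.526/0.58 = 0.907. The noncentrality is 0.907 × √(n/2), which is 2.87 at n = 20 and 2.72 at n = 18. Degrees of freedom are 3n − 3. The Tukey critical value is the 95% point of the studentized range for three groups divided by √2: 2.406 at n = 20 and 2.414 at n = 18. The unadjusted formula uses 1.96. The noncentral t distribution gives the ungated column below. Requiring a significant ANOVA first was simulated with 200,000 runs per scenario, with B equal to C, midway between C and A, or equal to A.

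| n per group | Tukey, ungated | Tukey after significant ANOVA |
|---|---|---|
| 20 | 67.7% | 66-67% |
| 18 | 62.2% | 61-62% |

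The 18 per group is an assumption: 20 × 0.9, reading the 10% as expected loss and taking imputation not to restore the lost information. A Bonferroni correction for three pairs would give 65.6% at n = 20. For scale, ungated Tukey power passes 80% at 26 evaluable per group (80.8%; 79.0% at 25).

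**3. Other targets at n = 20.** These depend on where physiotherapy lies, and the documents give no expected value for it.

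| Target | B equal to C | B midway |
|---|---|---|
| ANOVA significant | 83% | 71% |
| A significantly different from at least one of B and C (ANOVA, then Tukey) | 81% | 68% |
| A significantly different from both B and C (ANOVA, then Tukey) | 53% | 16% |

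At n = 18 the ANOVA figures are 78.5% and 65%.

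**4. Unadjusted pairwise tests after a significant F.** With exactly three groups this is a closed procedure. If all means are equal, nothing is tested unless F is significant. If only two are equal, only one true null remains. Simulation gave about 5% for any rejection when all means are equal, and about 5% for a false B-against-C finding when A differs and B equals C. A-against-C power with B anywhere from C to A was about 69-76% at n = 20 and 64-71% at n = 18.

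**5. Scale.** The sizing inputs are score units that decrease with improvement. The defined variable is an increase, read from a goniometer in degrees. No difference or SD in degrees is given, so steps 1 to 4 describe the score only.

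**The case against.** **Tukey is only an example.** The wording does introduce it that way, and the ANOVA is the only test firmly fixed. A reader might infer that the analysis as a whole delivers only 67%. The documents do not support that: the ANOVA has about 83% power if physiotherapy equals nasal oil, close to what is claimed. But that drops to about 71% with physiotherapy midway, and a significant F does not say which treatment is best, which is the stated aim. Bonferroni would not do better than Tukey.

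**The 10% is not a dropout forecast.** The sentence is loosely worded and gives no attrition rate. The 61-62% is therefore conditional on reading it that way; the 66-68% is not.

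**The hypothesis has about even odds.** One might infer this from the 53%, but that holds only if physiotherapy equals nasal oil. It is 16% if physiotherapy lies midway, and the documents fix neither case.

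**If the inputs are on the wrong scale, 67% means no more than 80%.** This stands. The restated figure must carry that condition. That the score is an ordinal grade is a natural inference, but the article does not say so; the mismatch with degrees is plain without it.

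**Covariate adjustment might recover power.** It is used only if needed and no baseline correlation is given, so no gain can be credited.

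**The small sample is admitted.** The Discussion does so with respect to generalizability, and leaves the power claim as it is.

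**Conclusion.** The point holds as a mismatch between design and analysis. The sample-size arithmetic itself is right. The 80% applies to one unadjusted comparison of microcautery with nasal oil. For that pair, ANOVA followed by Tukey gives about 66-68% at 20 per group, a shortfall of about 12 to 14 points, and about 61-62% at 18 per group. These figures assume normal outcomes with a common SD of 0.58, a true difference of 0.526 and Tukey as the post hoc test; the last pair also assumes 10% loss. They apply to the abduction score. For abduction in degrees the article shows no power at all, so the scale mismatch has to be settled together with the power figure. This should be fixed. It does not undermine the choice of ANOVA or call for a larger trial.

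**What to change.** 1. In the Sample Size section, state the power for the planned pairwise test: about 67% for microcautery against nasal oil at 20 per group, and about 62% if 10% are lost, conditional on the score-scale inputs. Qualify the statements about adequate power and reliable detection accordingly.
2. Either give the difference and SD in degrees and recompute, or state that the powered outcome is the abduction score and how it is derived from the goniometer reading.
3. Say whether the 10% is an expected loss.
4. Optionally, specify unadjusted pairwise tests after a significant F. This keeps family-wise error at 5% for three groups, but only within one outcome at one time point; the plan has four outcome measures and three follow-up visits. Power for the sized pair rises to about 69-76% at n = 20 (64-71% at n = 18) with physiotherapy between the other two arms, still below 80%. The Results section reports 16 recruited and analysis in progress, so the change must be dated and made before anyone examines outcome data by arm.

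The cost is protocol wording and a less favourable power figure. No further patients are needed.

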#### Minimum Sample Size Required

Based on expected differences, variability, significance level, and power, the minimum sample size required was calculated to ensure reliable detection of a meaningful improvement:

n=1=2=2 × (1.96 + 0.84)^2^ × (0.58)^2^/(0.526)^2^=20 per group

Total samples = 20 × 3 per group=60

### Randomization and Allocation

Computer-generated random numbers will be used to create a randomization chart. The participants will be randomized at a ratio of 1:1:1. To guarantee that treatment assignments are balanced, allocation sequence creation will be conducted using permuted blocks and provided in a randomized table. The researcher will enroll and give the participants an intervention and allocation sequence.

### Study Procedure

#### Overview

Before any activities related to the trial are initiated, participants or their guardians will be provided with verbal and printed information about the study. The investigator will ensure that they fully understand the study’s objectives, procedures, possible discomforts, and expected benefits. Participation shall be voluntary, and participants shall retain their right to withdraw from the trial at any time without prejudice.

After screening, suitable patients will be included in the study after signing the consent form. A required examination will be conducted. If the patients fall within the inclusion criteria, they will be included in the study with that day written down as day 1 or the baseline visit. They will be administered the treatment after completing all the formalities according to the protocol. Participants will visit the study site on procedure days and follow-up days during the trial. The activity details during each visit are shown in Table 6 and Figure 1.

**Table 6. T6:** Study schedule.

Component	Screening (day X)^a^	Baseline (day 0)	Day 1	Days 2-6	Day 7	Day 8	Day 16	Day 32
Informed consent	✓							
Demographic information and medical history		✓						
Assessment of *prakriti^b^*		✓						
Clinical examination	✓	✓	✓	✓	✓	✓	✓	✓
Honey thermal microcautery			✓		✓			
Standard physiotherapy			✓	✓	✓			
*Sida cordifolia* oil administration via nasal route			✓	✓	✓			
Placebo capsule issue			✓					
Assessment of adverse reactions			✓	✓	✓	✓		
Follow-up visit						✓	✓	✓

a Day X refers to the variable screening day when a participant is evaluated before the official baseline (day 0) of the study.

b Body constitution

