### Rationale of the Study

The 3 arms in our study were selected considering their unique mechanisms of action to adequately treat FS. Honey thermal microcautery is an Ayurvedic treatment with thermal effects. Standard physiotherapy is the classic gold standard, ensuring a robust comparator. *Sida cordifolia* oil via nasal route was selected considering its efficacy for *vata-kapha* disorders, particularly musculoskeletal diseases. These treatments were selected considering the evaluation and comparison of diverse approaches between modern medicine and traditional medicine toward optimal outcomes.

No study has been published comparing honey thermal microcautery, standard physiotherapy, and *S cordifolia* oil nasal administration. Additionally, no study has explored the use of honey thermal microcautery in FS. Considering these gaps, this study is essential to determine the most effective and safe therapeutic approach for FS, evaluating interventions such as honey thermal microcautery, standard physiotherapy, and *S cordifolia* oil nasal administration to identify treatments that optimize recovery time and minimize associated concerns.

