## Methods

### Overview

This study is an interventional, randomized, single-blind (assessor), 3–parallel arm study to compare the efficacy of honey thermal microcautery versus standard physiotherapy versus *S cordifolia* oil via nasal administration in the management of FS. We will intervene using honey thermal microcautery 2 times (the first and seventh day) along with placebo capsules twice daily for 7 days. Standard physiotherapy will be administered once a day along with placebo capsules twice daily for 7 days. *S cordifolia* oil via nasal administration will be administered via 8 drops in each nostril along with placebo capsules twice daily for 7 days. Follow-up will be conducted on the 8th, 16th, and 32nd days. Placebo capsules will be administered to reduce the psychological effect that patients might feel from knowing that they are not receiving any oral medicine, especially in the honey thermal microcautery group, where the treatment is administered only 2 times a week.

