### Intervention Description

This study involves 3 groups, each with specific treatment protocols, shown in Table 1. All 60 eligible participants will be thoroughly informed about the study protocol, and their consent will be obtained. They will be randomly divided into 3 groups: group A, group B, and group C. In group A, participants will receive honey thermal microcautery 2 times (first and seventh days) and placebo capsules for 7 days. Group B will receive standard physiotherapy once a day along with placebo capsules for 7 days. Group C will receive *S cordifolia* oil via 8 drops in each nostril and placebo capsules for 7 days. All baseline parameters will be recorded at the beginning of the trial. This study conforms to the SPIRIT guidelines, ensuring standard execution and ethical handling of the clinical trial. Placebo capsules will be identical in appearance, taste, and administration schedule to mimic a real medication. These will be administered alongside the active intervention twice daily after food, ensuring blinding and consistency throughout the study.

**Table 1. T1:** Grouping and posology.

Group	Intervention	Dose and frequency	Procedure time (min)	Duration (d)	Follow-up
A	Honey thermal microcautery+placebo	2 times a wk	20-30	2 (first and seventh)	On the 8th, 16th, and 32nd days
B	Standard physiotherapy+placebo	Once a day (in the morning)	30-60	7	On the 8th, 16th, and 32nd days
C	*Sida cordifolia* oil via nasal route+placebo	8 drops once a day	20-30	7	On the 8th, 16th, and 32nd days

Study drugs will be stored in a secure location and administered to the participants only under the direction of the investigator. Drug dispensing records will be kept. Any imbalance in the quantities dispensed and returned will be explained.

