#### Overview

Ethics approval from the Institutional Ethics Committee of Mahatma Gandhi Ayurved College Hospital and Research Centre was received (MGACHRC/1EC/Sep-2023/74) on September 18, 2023. The Clinical Trials Registry India registration number for this study is CTRI/2023/11/059594. The committee will oversee the trial’s advancement and determine its conclusion. The researcher shall evaluate any unfavorable event and report it to the ethics committee. The participants will be provided with written research details in 2 languages (Marathi and English), and written consent will be obtained from the participants on an informed consent form. They will be informed about the confidentiality of their details. Safety will be monitored by recording any adverse events during the entire study. We will make sure that no photos include any identifiable participants.

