#### Intervention Modification

Any negative effects noted during the treatment will be recorded and immediately reported to the ethics committee. The patients will receive the necessary treatment for the negative effects. If participants opt out of the treatment, they will be asked why, and this will be carefully documented.

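### Table 6 schedules adverse-reaction assessment on Days 1 to 8 only and leaves it out at the Day 16 and Day 32 visits, contradicting the promise to record adverse events throughout the study

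*Protocol article*

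**What the plan says.** Table 6 is the visit-by-visit schedule, and the text before it points to it (with Figure 1) for what happens at each visit. Its row "Assessment of adverse reactions" is ticked for Day 1, Days 2-6, Day 7 and Day 8. The Day 16 and Day 32 cells are blank. Both days carry ticks for clinical examination and for a follow-up visit.

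Participants attend in person on those days: "Participants will visit the study site on procedure days and follow-up days during the trial". The Methods overview fixes the visits: "Follow-up will be conducted on the 8th, 16th, and 32nd days". Participant Timeline With Deliverables confirms where the study ends for each participant: "the treatment period will last 7 days, and the last follow-up will be on the 32nd day".

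The safety text uses different windows. Under Ethical Considerations, Overview: "Safety will be monitored by recording any adverse events during the entire study". Under Intervention Modification the window is treatment only: "Any negative effects noted during the treatment will be recorded and immediately reported to the ethics committee". AR Management speaks of reactions at any time in the trial.

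Intervention Description gives the days of the invasive procedure: "In group A, participants will receive honey thermal microcautery 2 times (first and seventh days) and placebo capsules for 7 days". The Rationale names safety as a reason for the study: "this study is essential to determine the most effective and safe therapeutic approach for FS".

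**The concern.** A schedule with its own adverse-reaction row tells site staff when to make that assessment. Here the row stops at Day 8, while the ethics text promises recording to the end. Staff cannot follow both, and the safety wording elsewhere does not settle which window applies.

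The visits left out matter most for group A. That group is treated with a heated metal rod, the number of applications is not fixed in advance, and the second session is on Day 7. The protocol admits patients with controlled type 2 diabetes and allows anticoagulants to continue. If a problem at the treated site, or any other reaction, appeared after Day 8, the schedule would not prompt anyone to ask about it. Ascertainment would be scheduled up to Day 8 and incidental afterwards. The Rationale says that no study has explored this procedure in frozen shoulder, so harms information from this trial has particular value.

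**Working it through.** There is no stated safety figure to reproduce. The check is a reading of Table 6 against the text, followed by counts.

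**Relevant rows of Table 6**

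| Row | Day 1 | Days 2-6 | Day 7 | Day 8 | Day 16 | Day 32 |
|---|---|---|---|---|---|---|
| Clinical examination | yes | yes | yes | yes | yes | yes |
| Thermal microcautery | yes | – | yes | – | – | – |
| Adverse-reaction assessment | yes | yes | yes | yes | – | – |
| Follow-up visit | – | – | – | yes | yes | yes |

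The follow-up row lines up with the three days named in the Methods overview, so the blank cells are not a fault in how the table was read from the PDF.

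**Counts**

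1. Follow-up visits: Days 8, 16 and 32. With an adverse-reaction assessment: Day 8 only, so 1 of 3. Without: 2 of 3.
2. Attendance days from Day 1, taking Table 6 as it stands for all groups: Days 1 to 8, 16 and 32, so 8 + 2 = 10. With the assessment: 8 of 10 (80%). Without: 2 of 10.
3. Interval from the last scheduled assessment to the last visit: 32 − 8 = 24 days.
4. Interval from the second microcautery session to the omitted visits: 16 − 7 = 9 days and 32 − 7 = 25 days. The one later scheduled assessment comes at 8 − 7 = 1 day.

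**Assumption behind count 2.** Table 6 is not split by group. If group A attended only on its procedure and follow-up days (Days 1, 7, 8, 16 and 32), the count for that group would be 2 of 5 without the assessment. The daily checks described under Strategies to Improve Adherence to the Study Protocol, and the Days 2-6 ticks, favour the reading with ten days. Count 1 is the same either way.

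**Texts side by side.** The ethics text sets the period for recording adverse events as the whole study, and the timeline puts the last follow-up on Day 32. The table ends scheduled assessment on Day 8. Under the first, Days 16 and 32 fall within the safety period. Under the second, they have no adverse-reaction activity.

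**The case against.** The strongest reply is that a blank cell is not a ban on recording. The ethics text commits to recording any adverse event. A clinical examination takes place at both late visits, and the investigator must record any medication other than the protocol drugs, which could also reveal a problem. Figure 1 and the case report form are not shown and may provide for it. This stands as far as it goes: late harm could be picked up, and it would be wrong to say that it will be lost. It does not remove the contradiction. The clinical examination is ticked in every column, screening included, and adverse reactions have a row of their own. The schedule treats them as separate activities, and the second one stops.

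A reader might infer more than the document supports:

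- **That safety goes unobserved for 24 of 32 days.** Most of those days have no visit in any case. The fair measure is visits: two of ten, or two of three after Day 7.
- **That harm after the second session is asked about only once.** Day 7 also carries a tick, and the document does not say whether that check precedes or follows the procedure. There may be a same-day check as well. The first session, on Day 1, is followed by scheduled assessment through Day 8.
- **That the result is biased in favour of microcautery.** This is plausible but not shown. The schedule is the same for all groups, and the document gives no rate or timing for late reactions. Diabetes must be controlled (fasting up to 140 and postprandial up to 180 mg/dL), and patients unfit for cauterization are excluded.
- **That a stated safety objective is compromised.** Safety appears in the Rationale. The objectives and the Outcomes section concern efficacy and sustained relief, and no between-group safety comparison is stated there.

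One practical objection also stands. Days 16 and 32 are efficacy visits in an assessor-blind trial. If the blinded assessor inspected the treated site, group A allocation could be revealed.

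**Conclusion.** The contradiction is real and should be corrected. Table 6 omits adverse-reaction assessment at two of the three follow-up visits, while the ethics text promises recording for the whole study. After the day of the second microcautery session, the only scheduled assessment is one day later. Events after Day 8 would then be found only through the general examination or if volunteered.

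Its size is two of ten attendance days from Day 1, assuming that all groups attend as Table 6 is ticked. No sample size, planned test or efficacy estimate depends on it. The conclusion is that later harm is under-ascertained relative to what the protocol promises. It does not extend to a demonstrated bias between groups. It rests on taking Table 6 as the working schedule, as the Study Procedure text directs, and on Figure 1 not adding an assessment that the table leaves out.

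**What to change.** In Table 6, tick the adverse-reaction row at Day 16 and Day 32, so that the schedule matches Ethical Considerations. Align the safety wording under Intervention Modification, which now speaks of treatment only, with the same window. Ask about reactions in the same way in all three groups. Do this after the efficacy ratings have been recorded, or have existing staff other than the blinded assessor do it, so that sight of the treated site does not reveal allocation.

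Stating a shorter assessment window in the ethics text would also make the document consistent. It would give up safety information at visits that already take place, so it is the weaker choice.

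The cost is small: a case report form page at two visits that participants already attend, and some care over the order of assessments. With 16 of the 60 planned participants recruited by January 2025, a correction made at that point would still have covered at least the remaining 60 − 16 = 44. The change concerns data capture only and alters no treatment rule.
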